## Abstract

**Background:**

There is a growing debate on the relationship between health-related quality of life (HRQoL) and patient survival which has been going on for the last few decades. The greatest wish of clinicians is to extend the latter while improving the former. Following neck dissection of early-stage oral carcinoma, “shoulder syndrome” appears due to traction of the accessory nerve during removal of level IIb, which greatly affects patient quality of life. Since occult metastasis in level IIb of early-stage oral carcinoma is extremely low, some surgeons suggest that level IIb can be exempt from dissection to improve the HRQoL. However, other surgeons take the opposite view, and thus there is no consensus on the necessity of IIb dissection in T1–2N0M0 oral squamous cell carcinoma (OSCC).

**Methods:**

We designed a parallel-group, randomized, non-inferiority trial that is supported by Shanghai Ninth People’s Hospital, Shanghai Jiao Tong University, School of Medicine, Shanghai, China. We will enroll 522 patients with early oral carcinoma who match the inclusion criteria, and compare differences in 3-year overall survival, progression–free survival (PFS) and HRQoL under different interventions (retention or dissection of level IIb). The primary endpoints will be tested by means of two-sided log-rank tests. Analysis of overall and progression-free survival will be performed in subgroups that were defined according to stratification factors with the use of univariate Cox analysis. In addition, we will use post-hoc subgroup analyses on the basis of histological factors that were known to have effects on survival, such as death of invasion of the primary tumor. To evaluate HRQoL, we will choose the Constant–Murley scale to measure shoulder function.

**Discussion:**

Currently, there are no randomized controlled trials with large sample sizes on the necessity of IIB dissection in T1–T2N0M0 OSCC. We designed this noninferiority RCT that combines survival rate and HRQoL to assess the feasibility of IIb neck dissection. The result of this trial may guide clinical practice and change the criteria of how early-stage oral cancer is managed. The balance between survival and HRQoL in this trial is based on early-stage breast cancer treatment and may provide new ideas for other malignancies.

**Trial registration:**

Chinese Clinical Trial Registry, ChiCTR1800019128. Registered on 26 October 2018.

**Electronic supplementary material:**

The online version of this article (10.1186/s13063-019-3683-y) contains supplementary material, which is available to authorized users.

## Background

The surgical treatment of early-stage oral squamous cell carcinoma (OSCC) has been a dilemma for decades. In 2015, Anil K. D’Cruz published a randomized trial on the relationship between overall survival (OS) and the quality of life in patients who underwent two types of surgery for early-stage OSCC. The study demonstrated that the 3-year OS was greatly improved when patients underwent neck dissection and primary resection at the same time, compared with those who underwent primary resection but not neck dissection [1]. However, if we only pursue a higher survival rate, most patients will be regarded as ‘overtreated’. At present, the technique for detecting occult metastatic lymph nodes in the neck is still imprecise; we can detect susceptible nodes only by physical examination, B-scan ultrasonography, and enhanced computed tomography (CT)/magnetic resonance imaging (MRI), but diagnoses obtained by these methods are far from precise [2, 3]. Studies have shown that the rate of occult metastasis in the early stages of oral cancer is about 30% [1, 4, 5], meaning that nearly 70% of patients with negative nodes underwent neck dissection during routine treatment.

At present, we aim to extend survival and at the same time improve health-related quality of life (HRQoL) [6, 7]. After neck dissection, shoulder weaknesses such as dyskinesia, trapezius atrophy, loss of shoulder abduction, and shoulder and neck pain will occur; collectively, these are called ‘shoulder syndrome’ [8–10]. The physiological mechanism of this symptom is still unclear, but it can be explained anatomically. The accessory nerve innervates the sternocleidomastoid and trapezius muscles [11]; once the nerve is pulled during surgery, the function of both muscles is affected, and symptoms correspondingly occur. In addition, direct traction during surgery of the sternocleidomastoid muscle and other muscles associated with shoulder movement can damage the muscle bundle [10]. Therefore, shoulder syndrome can greatly affect postsurgical HRQoL. If the accessory nerve can be protected or the pulling of it avoided during surgery, shoulder syndrome will be greatly controlled.

The accessory nerve divides level II in the neck into two sublevels, level IIa at the front and level IIb at the back. In IIb dissection, the accessory nerve must be pulled, which causes injury to the nerve. It has been reported that the rate of IIb metastasis in early-stage oral cancer is extremely low at no more than 6% [5, 12–17]. Some clinicians therefore suggest that level IIb be exempted from neck dissection in early OSCC in order to improve HRQoL [5, 8, 17]. However, others disagree, and thus there is no consensus about the necessity of IIb dissection in T1–2N0M0 OSCC.

To assess whether IIb neck dissection should be performed in T1–T2 N0 OSCC, and its effects on OS and HRQoL, we designed this parallel-group, randomized, noninferiority trial according to the SPIRIT 2013 checklist (Additional file 1).

## Methods

### Study aims and design

Before designing this protocol, we searched the PubMed database for randomized controlled trials (RCTs) of IIb neck dissection in early-stage oral cancer on 30 May 2018, but we found no results. We repeated the search on 26 November 2018 using the keywords “IIb” and “neck” and searching only in English. We found only one RCT with a small sample size from 2018, and six prospective analyses of IIb after neck dissection from 2004 to 2018. In addition, we found two retrospective systematic reviews and meta-analyses. All of the above indicated that the rate of IIb metastasis in early-stage oral cancer is extremely low at no more than 6%. However, there is still no strong evidence to prove the necessity of IIb dissection in T1–T2N0M0 OSCC.

We are conducting a parallel-group, noninferiority randomized trial to assess whether IIb neck dissection should be performed in T1–T2 N0 OSCC and its impacts on OS and HRQoL. Our study plan is summarized in Fig. 1.

**Fig. 1 Fig1:**
[figure not shown]
Trial profile

### Eligibility criteria

In this prospective, randomized, noninferiority trial, only patients who are in the clinical stages of T1–2N0M0 according to the American Joint Committee on Cancer (AJCC) Cancer staging manual, 8th edition [18], will be enrolled. Based on the National Comprehensive Cancer Networks (NCCN) guideline [19], the treatment of T1–T2 N0 oral cancer is primary resection with or without ipsilateral or bilateral cervical lymph node dissection or sentinel lymph node biopsy, and the use of radiotherapy or chemotherapy is decided according to the specific circumstances. Patients with T2+ stage oral cancer are often recommended for postoperative radiotherapy [19] and a broader range of neck dissection. Radiation may affect the sensory and motor function of the shoulder, and it has been shown that > 90% of breast cancer patients have shoulder pain and motor dysfunction after radiotherapy [20]. The probability of neck occult lymph node metastasis is greatly improved if clinical T stage is greater than 2 [17]. Therefore, we will enroll patients in stage T1 or T2. There may be discrepancies between postoperative pathological T (pT) stage and clinical T (cT) stage as some tumors can be presurgically diagnosed as T1 or T2 but have stage T3 confirmed after surgery because of the deep infiltration depth. We decided to enroll these patients. The principle for treatment of tumors located in an oral cavity site such as the soft palate, tonsil or root of the tongue differs from that for oral cancer [19]. Although it is reported that level IIb of the neck can be preserved in T1–T2 N0 oropharyngeal cancer [21, 22], such patients will not be enrolled. We will eliminate all patients in stage cN+ because the possibility of the occult metastasis in IIb increases [17]. Neck status is usually evaluated by bilateral cervical B-scan ultrasound and enhanced CT/MRI. Patients who have no suspicious lymph nodes will be enrolled after all such examinations have been conducted. In addition, patients with distant metastases will not be enrolled.

Inclusion and exclusion criteria are summarized in Table 1.

**Table 1 Tab1:**
[figure not shown]
Eligibility criteria

### Interventions

After randomization, the two groups will be allocated to different interventions (see Table 2 for details). Primary resection will be 1.5–2 cm away from the tumor, and the negative margin must be obtained. If suspicious nodes in level III are found during neck dissection, and metastasis is confirmed according to the examination of frozen biopsies, we will expand neck dissection to level IV or V. For the IIb retention group, if a suspicious positive lymph node is found in level IIa during surgery and metastasis is confirmed by frozen examination, both level IIa and IIb must be dissected [5, 13].

**Table 2 Tab2:**
[figure not shown]
Interventions in different groups

All our surgical treatments will be based on the NCCN baseline.

### Outcomes

#### Primary outcome: overall survival (OS)

We will use the 3-year OS after surgery as the primary outcome, and follow-up at 3 months, 6 months, 1 year, 1.5 years, 2 years, 2.5 years and 3 years after surgery (Fig. 2).

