#### Randomization

This is the starting point of our trial, indicating when patients officially enter the trial. Patients will be enrolled in the IIb retention or IIb dissection group according to the repeatable randomized number table.

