#### Intervention

The number of patients who must be removed from our trial for any reason during intervention (surgery) will be represented as *m*_2_, and the number of patients during follow-up will be represented as *n*_3_ = *n*_2_ − *m*_2_.

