#### Follow-up

Follow-up timepoints include immediately, 7 days, 1 month, 6 months, 1 year, 1.5 years, 2 years, 2.5 years and 3 years after surgery. Follow-up will include physical examination, enhanced CT/MRI, bilateral neck B-scan ultrasonography, Constant–Murley score and a safety observation. There will be different evaluations at different timepoints, but overall evaluation will be the same between the two groups. The number of patients who quit our trial for any reason during follow-up will be represented as *m*_3_, and the number of patients who will be included in our analysis will be represented as *n*_4_ (see Fig. 3 for details).

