### Sample size

In calculating the sample size, we assumed the 3-year OS rate in the IIb retention group will be about 78%, α = 0.05 (one-sided), power of 80% (β = 20), and that in the IIb dissection group will be 80% [1]. The noninferiority margin will be 12%, so the sample size as generated by PASS Sample Size Software 15.0 (NCSS LLC, Kaysville, Utah, USA) will be 261 for IIb retention and 260 for IIb dissection. To obtain a reasonable sample size and make sure the trial is instructive for clinical work, we combined the common opinions of oral and maxillofacial experts, and the statistician defined the noninferiority margin as 12% [24]. Although the value seems to be large, its role is to control the large sample size that would otherwise be unapproachable.

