#### Secondary outcomes

For HRQoL, we will use the Constant–Murley scale to evaluate shoulder function at each follow-up timepoint. In order to improve the reliability of shoulder function evaluation, two clinicians will be systematically trained on use of the scale.

For PFS, observations will start at time of randomization and end when events (see below) occurred. In the period of time from randomization (Fig. 3) to any primary recurrence, local metastasis, distant metastasis, and other life-threatening events or death will be defined as PFS.

If a patient has not returned to the clinic for more than 2 months after the follow-up timepoint, a telephone inquiry will be conducted.

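### The primary endpoint, 3-year OS, is timed from surgery while PFS and trial entry are timed from randomisation: an inconsistent definition whose numerical effect is probably small

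*Protocol article*

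**What the plan says.** Four parts of the protocol article bear on the time origin.

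- **Outcomes, Primary outcome.** "We will use the 3-year OS after surgery as the primary outcome". The follow-up visits in the same sentence are also counted from surgery.
- **Data collection methods, Secondary outcomes.** "For PFS, observations will start at time of randomization and end when events (see below) occurred". The definition then runs: "In the period of time from randomization (Fig. 3) to any primary recurrence, local metastasis, distant metastasis, and other life-threatening events or death". Death is thus a PFS event.
- **Participant timeline, Randomization.** "This is the starting point of our trial, indicating when patients officially enter the trial".
- **Interventions.** "After randomization, the two groups will be allocated to different interventions". Randomisation and surgery are therefore separate events in a fixed order.

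The Intervention paragraph of the Participant timeline adds a removal step at surgery. It begins "The number of patients who must be removed from our trial for any reason during intervention (surgery) will be represented as" and gives these patients the symbol m2, so that n3 = n2 − m2 go forward to follow-up. The Blinding section says that surgeons and patients know the group.

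Nowhere does the article give OS a randomisation origin, and nowhere does it state the time between randomisation and surgery.

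**The concern.** Two endpoints that both end at death should share a starting point, and in a randomised comparison that point should be randomisation. Here the secondary endpoint has that origin and the primary endpoint does not.

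Three consequences follow from the text.

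1. A patient who dies after assignment but before the operation has a PFS event and no OS event.
2. A randomised patient who is never operated on has no date from which OS could run. Keeping everyone in the analysis set would not cure this by itself, because the clock never starts.
3. For a patient who dies without earlier progression, PFS equals OS plus the wait for surgery, so PFS is the longer of the two. Coherent definitions do not allow that.

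What is at stake is the protection that randomisation gives. The groups are comparable as randomised. Starting the clock at surgery compares only those who reach surgery, and the allocation is known by then.

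**Working it through.** **Step 1. The definitions side by side.**

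| | OS (primary) | PFS (secondary) |
|---|---|---|
| Start | surgery | randomisation |
| Death counts | yes | yes |
| Death before surgery | not covered | event |
| Never operated on | no start date | start date exists |
| Death without progression, gap g, death t after surgery | t | g + t |

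**Step 2. Inputs for scale.** From the Sample size section: 3-year OS of 80% (IIb dissection) and 78% (IIb retention), a margin of 12%, read as percentage points, and 261 and 260 patients. The article gives no figure for the gap or its effect, so the gap is assumed to be 1 to 8 weeks and the hazard constant.

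The arm size is used here only as a denominator. With unpooled variance, n = (0.80 × 0.20 + 0.78 × 0.22)(z_α + z_β)² / (0.12 − 0.02)². At one-sided 0.025 this is 0.3316 × 7.849 / 0.01 = 260.3, so 261 per arm. At the stated one-sided 0.05 it is 0.3316 × 6.183 / 0.01 = 205.01, so 206. That mismatch is a separate matter. The choice of time origin does not enter this formula.

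**Step 3. Expected deaths before surgery.** Monthly hazard h = −ln(S)/36, which is 0.00620 for S = 0.80 and 0.00690 for S = 0.78. A gap of w weeks is m = 7w/30.4375 months. Expected deaths per 261 patients = 261 × (1 − e^(−hm)).

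| Assumed gap | S = 0.80 | S = 0.78 |
|---|---|---|
| 1 week | 0.37 | 0.41 |
| 2 weeks | 0.74 | 0.83 |
| 4 weeks | 1.48 | 1.65 |
| 8 weeks | 2.96 | 3.29 |

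The range is about 0.4 to 3.3 deaths per arm.

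**Step 4. Effect of one missed death in one arm only.** If the patient stays in the denominator but the death is not counted, the arm's 3-year rate moves by 1/261 = 0.38 points. If the patient drops out of numerator and denominator, it moves by about 0.79/261 = 0.30 points, where 0.79 is the mean of the two planning rates.

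**Step 5. Against the margin.** At 8 weeks the expected numbers differ between arms by 3.29 − 2.96 = 0.33 deaths, or 0.33 × 0.38 = 0.13 points. If 3.3 deaths were missed in one arm and none in the other, the shift would be 3.3 × 0.38 = 1.3 points, about a tenth of the 12-point margin.

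**The case against.** The best defence is that the sentence on the primary outcome is condensed. It names a 3-year milestone and a visit schedule, and a fuller protocol or SAP may set the formal start. The figures showing the timeline are also not visible here. This has some force. But the words after surgery are attached to the 3-year OS itself before the visits are listed, and the article does state an origin for PFS. An analysis plan that timed OS from randomisation would still contradict the stated endpoint, so the sentence would need correcting either way.

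Several limits on the point stand.

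- **Unequal loss by arm is not shown.** A reader might infer that knowledge of the group leads to more delay or refusal in one arm. The documents do not support that: both arms have primary resection and neck dissection, and the tested difference is level IIb.
- **A false claim of non-inferiority is not shown.** Deaths before surgery cannot be caused by retaining or dissecting IIb. If they are balanced, counting them does not strengthen a non-inferiority test. For operated patients under constant hazard, a window moved by the gap has the same expected 3-year rate, since S(g + 36)/S(g) = S(36).
- **Counts of unoperated patients do not enlarge the effect.** One might assume that 1 to 3% of 521 patients, or 5 to 16, never reach surgery, and set this beside the planned excess of 0.02 × 261 = 5.2 deaths. The percentage has no source in the documents, and patients are not deaths. At 20 to 22% three-year mortality, they imply only about 1.0 to 3.4 deaths over both arms together.
- **Part of the problem lies elsewhere.** Patients lost around surgery are also affected by the m2 removal, which a new OS definition does not undo.
- **The two endpoints are tested separately.** PFS exceeding OS is a mark of incoherent definitions and distorts no planned test by itself.

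**Conclusion.** The inconsistency is real and lies in what the article states: OS from surgery, PFS from randomisation, and randomisation as trial entry. It makes the primary comparison conditional on an event after assignment in an unblinded trial, and it leaves some randomised patients without a defined primary outcome.

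Its size is probably small, on the assumptions of a 1 to 8 week gap and a constant hazard at the planning rates. A much longer gap, or loss that depends on the arm, would change that, but the documents give no evidence of either. The point therefore concerns a sound and consistent definition of the primary endpoint. It does not show that the trial's result would be biased. It is worth correcting because the correction is cheap.

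**What to change.** In the Primary outcome section, define OS as the time from randomisation to death from any cause, and read the 3-year rate at 36 months from randomisation in both arms, the same origin as PFS.

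Visits can stay scheduled from surgery. With a gap g, the 3-year contact after surgery falls at 36 months + g from randomisation, so month 36 is already covered for every operated patient and no extra contact is needed for them. Patients without surgery need telephone survival contacts timed from randomisation.

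For the full benefit, the Participant timeline should also say that patients counted in m2 stay in the OS analysis.

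The cost is one changed sentence in the endpoint definition, one sentence on m2, and a small contact schedule for unoperated patients. The randomisation date is already needed for PFS, survival status is already collected by telephone, and the sample size does not change.

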**Fig. 2 Fig2:**
[figure not shown]
SPIRIT figure, trial visits and assessments. CT computed tomography, MRI magnetic resonance imaging

#### Secondary outcomes

The secondary outcomes are HRQoL and progression-free survival (PFS). For HRQoL, we will use the Constant–Murley scale to evaluate patients’ shoulder function, with follow-up at 7 days, 21 days, 3 months, 6 months, 1 year, 2 years and 3 years after surgery.

There are many reasons for setting OS as the primary outcome. First, it is widely used as a reliable indicator for evaluating the prognosis of tumors. It is reported that the 3-year OS rate in an IIb dissection group is about 80% [1], which includes disease-free survival and living with disease. Metastasis in level IIb is extremely low, and even if it happens it is nonlethal and can be instantaneously controlled by surgery or radiotherapy. Theoretically, 3-year OS in the IIb retention group will resemble that in the dissection group. A summary of 38 RCTs [7, 23] reports no significant association between PFS duration and HRQoL. In addition, as PFS is not as reliable as OS and can also increase difficulties in follow-up, we did not use PFS as the primary outcome.

### Participant timeline

#### Recruitment

Patients will be preliminary screened at the clinic. The number of all eligible patients will be represented as *n*. After eligibility screening, we will record the number of cases that do not meet inclusion criteria as *m*, and the number of patients to be enrolled will be represented as *n*_1_ = *n* − *m*. The number of patients who are not willing to sign the informed consent form will be recorded as *m*_1_ and will be excluded. All patients (*n*_2_ = *n*_1_ − *m*_1_) who consent to participate will be randomized according to a repeatable randomized number table produced by statisticians.

#### Randomization

This is the starting point of our trial, indicating when patients officially enter the trial. Patients will be enrolled in the IIb retention or IIb dissection group according to the repeatable randomized number table.

#### Intervention

The number of patients who must be removed from our trial for any reason during intervention (surgery) will be represented as *m*_2_, and the number of patients during follow-up will be represented as *n*_3_ = *n*_2_ − *m*_2_.

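### The participant flow removes patients after randomisation before reaching the number analysed, so as written the overall survival comparison is not as-randomised; the size and direction of any bias are unknown

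*Protocol article*

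**What the plan says.** All references are to the protocol article.

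- **Participant timeline, Randomization:** randomisation is the point at which a patient officially enters the trial. The number randomised is n2.
- **Participant timeline, Intervention:** the symbol m2 is defined by the words "The number of patients who must be removed from our trial for any reason during intervention (surgery"). Those in follow-up are then n3 = n2 − m2.
- **Participant timeline, Follow-up:** the symbol m3 is defined by the words "The number of patients who quit our trial for any reason during follow-up". The last symbol, n4, is introduced separately: "the number of patients who will be included in our analysis will be represented as". The text refers to Fig. 3 for details; that figure is not available here.
- **Interventions:** the retention arm has an intraoperative conversion rule of its own, which opens "For the IIb retention group, if a suspicious positive lymph node is found in level IIa during surgery". Once frozen section confirms metastasis, level IIb is dissected as well.
- **Outcomes, Primary outcome:** "We will use the 3-year OS after surgery as the primary outcome".
- **Data collection methods:** "For PFS, observations will start at time of randomization". Survival status is collected by telephone at each timepoint.
- **Blinding:** surgeons and patients know the allocation.
- **Adverse events:** death during surgery is among the foreseen events.

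No section says that patients are analysed in the arm to which they were randomised, or that the reduced set is a secondary per-protocol population.

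**The concern.** Removals at surgery and during follow-up both come after randomisation. If the primary analysis is run on n4 as the text describes it, the arms compared are no longer the randomised arms. Three features make that more than a formality here.

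1. A death during surgery is a primary-endpoint event, yet the definition of m2 is wide enough to take it out of the comparison. Timing overall survival from surgery, while progression-free survival runs from randomisation, adds to the uncertainty about early deaths.
2. Surgeons know the allocation, and only the retention arm has the conversion after a positive IIa node. The chance of being removed at surgery could therefore differ by arm.
3. The article describes n3 as the patients in follow-up. Read literally, survival is not collected for those removed at surgery, and later analysis wording could not recover it.

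In a non-inferiority trial, losing poor-prognosis patients from the experimental arm alone would make the claim easier to reach.

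**Working it through.** **Inputs from Sample size:** 3-year survival 78% (retention) and 80% (dissection), margin 12 points, one-sided alpha 0.05, power 80%, 261 and 260 patients. No allowance for loss is stated.

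**Reproducing the plan's figure.** With unpooled variance,

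n per arm = (z₁₋α + z₀.₈₀)² × [0.80×0.20 + 0.78×0.22] / (0.12 − 0.02)²

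- One-sided 0.025: raw 260.3, so 261. This matches.
- One-sided 0.05, as stated: raw 205.0, so 206. This does not match.

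The alpha label is a separate matter, but it decides which power figures apply below.

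**Error scenarios.** The documents give neither removal rates nor the prognosis of those removed, so f and q are assumptions. Let true survival be 68% v 80%, exactly at the margin. A share f of the retention arm only, with 3-year survival q, is removed.

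Apparent retention survival: p = (0.68 − f·q)/(1 − f)

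Standard error: SE = √[p(1−p)/(261(1−f)) + 0.80×0.20/260]

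Chance of wrongly claiming non-inferiority: Φ((p − 0.68)/SE − z₁₋α)

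| f | q | p | Shift (points) | Error, one-sided 0.025 | Error, one-sided 0.05 |
|---|---|---|---|---|---|
| 5% | 60% | (0.68−0.03)/0.95 = 68.4% | +0.4 | 3.2% | 6.2% |
| 10% | 50% | (0.68−0.05)/0.90 = 70.0% | +2.0 | 7.4% | 12.9% |
| 15% | 50% | (0.68−0.075)/0.85 = 71.2% | +3.2 | 12.5% | 20.2% |
| any | 68% | 68.0% | 0 | about 2.5% | about 5% |

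**The opposite case.** Remove the same share from both arms, with q = 50% in each.

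- 5%: (0.68−0.025)/0.95 = 68.9% and (0.80−0.025)/0.95 = 81.6%. The difference is −12.6 points and the 0.025-level error falls to 1.7%.
- 10%: 0.63/0.90 = 70.0% and 0.75/0.90 = 83.3%. The difference is −13.3 points and the error is 1.1%.

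The sign therefore depends on who is removed and from which arm.

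**Power.** Power = Φ(0.10/SE − z₁₋α), with SE = √(0.1716/261 + 0.16/260) = 0.0357 at full size. Loss is taken as non-informative and equal in the two arms.

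| Loss | One-sided 0.025 | One-sided 0.05 (stated) |
|---|---|---|
| none | 80.0% | 87.7% |
| 10% | 75.8% | 84.5% |
| 20% | 70.8% | 80.6% |

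**The case against.** The strongest reply is that the n and m symbols are bookkeeping for a flow diagram. The Statistical methods section excludes nobody, and an article commonly leaves the definition of analysis populations to a fuller document. Part of this stands: the formula for n4 is not printed, so n4 = n3 − m3 is an inference. But the subtraction of m2 is printed, and the article itself names n4 as the number analysed. That is a stated rule and not merely a gap.

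Four stronger readings are tempting, and the documents do not support them.

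- **Quitters are deleted, not censored.** The text does not say so. A log-rank test ordinarily censors incomplete follow-up, and telephone collection of survival status points the same way.
- **Converted retention patients are removed.** The conversion is described as part of that arm's intervention, and nothing says that these patients leave the trial. The text simply does not settle their place in the analysis. Extension to further levels after a positive level III node is not limited to one arm.
- **The bias favours non-inferiority.** This needs selective removal of poor-prognosis patients from the retention arm. Symmetric removal pushes the other way.
- **Power falls below 80%.** This is so only at one-sided 0.025. At the stated one-sided 0.05, power stays above 80% even after a 20% loss.

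The difference in time origin is also minor on the evidence available. No interval from randomisation to surgery is given, and nothing suggests that deaths within it would differ by arm.

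**Conclusion.** The point holds in a limited form. Taken as written, the participant flow leads to an analysis set smaller than the randomised set, in an unblinded trial with survival as primary outcome, and deaths during surgery could be among those left out. This rests on the printed n3 = n2 − m2, on the natural but unprinted reading of n4, and on the absence of any as-randomised statement.

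The bias cannot be sized or signed from the documents. An error of about 3–12.5% against a nominal 2.5% is one conditional scenario: true survival at the margin, and 5–15% of the retention arm alone removed with 50–60% survival. Other patterns give no bias, or bias against non-inferiority. The fall in power to about 76% at 10% loss is likewise conditional, on one-sided 0.025. The case for changing the text does not depend on any of these figures: the wording permits arm-dependent exclusion, and survival data not collected for removed patients may be unrecoverable.

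**What to change.** State in the protocol and the analysis plan that:

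- the primary overall survival analysis and the progression-free survival analysis include every randomised patient in the assigned arm, with converted retention patients kept in the retention arm;
- time zero is randomisation for both endpoints;
- telephone follow-up of vital status continues for patients removed at surgery or withdrawn, where consent allows, and otherwise they are censored at last contact;
- a per-protocol analysis is reported in support of the non-inferiority claim;
- m2 and m3, with reasons by arm, serve only the flow diagram.

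The cost is small. This is mainly wording, and telephone survival follow-up is already planned. The added work is telephoning the patients removed at surgery or withdrawn. According to Trial status, enrolment had not begun at this protocol version, so for a trial at that stage the change can be in place before any patient is removed. No clinical management changes.
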